**Discussion:**

This is the first randomized phase 3 prospective trial designed to determine whether PSMA PET/CT molecular imaging can improve outcomes in patients with PCa early BCR following radical prostatectomy.

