We also assume that approximately 13% of subjects randomized to Arm 2 will have extra-pelvic metastasis detected by PSMA PET/CT, and therefore are not curable by SRT directed to the pelvis [38]. Hence the primary endpoint of the trial is the success rate of SRT. If PSMA PET/CT detects distant metastases, then local salvage with SRT is not a medically indicated therapy because it is not curative. It is therefore not standard-of-care to perform SRT in patients with evidence of distant metastases. The current standard-of-care is to offer SRT to patients who have no evidence of metastatic disease. We acknowledge that patients in the trial who do not undergo PSMA PET/CT may have “hidden/unknown” metastatic disease, but these patients would still receive SRT per routine care. An intention to treat analysis would classify subject who undergo PSMA PET/CT and are found to have distant metastases as failure even without having received treatment. Therefore, the primary endpoint of the trial is the success rate of SRT in patients who actually receive SRT. The question the trial asks is: “*Within patients for whom SRT is appropriate given the imaging results, is the rate of SRT success different between standard-of-care imaging and PSMA PET/CT arms?*”. As such, it would be inappropriate for patients who do not undergo SRT to be included for the primary endpoint. Therefore, patients with PSMA PET/CT showing distant metastases will not be included for the primary endpoint analysis but will still be followed. Based on these estimates, 193 subjects are required to be randomized in a 1:1.13 ratio (90 in control group and 103 in the PSMA group). Randomized, eligible, sample size in each group is therefore *n* = 90.

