### Outcome measures

#### Primary endpoint measure

Success rate of SRT measured as rate of biochemical progression-free survival (BPFS) after initiation of SRT (Time Frame: From date of initiation of SRT until the date of first documented progression or death from any cause, whichever comes first, assessed up to 5 years). Biochemical progression is defined as a serum PSA ≥ 0.2 ng/mL and rising after completion of SRT (second confirmatory value must be rising and separated by ≥ 1 month).

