### Sample size determination

In our a previous study [38], 52/270 patients (19%) had at least one lesion detected by PSMA PET/CT which was not covered by the standard radiation field that covered both the prostate bed and pelvic lymph nodes (RTOG consensus delineations). Standard SRT would not have resulted in durable disease control because gross disease would have been missed. Therefore, we hypothesized that the incorporation of PSMA PET/CT to SRT planning will improve 5-year PFS survival by 20%. Based on available published literature we estimated the 5 y PFS at 60% with standard SRT [5–9, 12]. Therefore, we assume 5-year PFS to be 60% in Arm 1 (standard SRT) and 80% in Arm 2 (PSMA PET/CT based SRT). We also assume that approximately 13% of subjects randomized to Arm 2 will have extra-pelvic metastasis detected by PSMA PET/CT, and therefore are not curable by SRT directed to the pelvis [38]. Based on these estimates, 193 subjects are required to be randomized in a 1:1.13 ratio (90 in control group and 103 in the PSMA group). Randomized, eligible, sample size in each group is therefore *n* = 90. When the randomized, eligible, sample size in each group is 90, with an estimated total number of events required of 46, an exponential maximum likelihood test of equality of survival curves with a 0.050 two-sided significance level will have 80% power to detect the difference between a PSMA group exponential parameter of 0.0446 (assuming a 5 year failure rate of 20%) and a control group exponential parameter of 0.1022 (assuming a 5-year failure rate of 40%), which equals a constant hazard ratio of 0.436; this assumes a maximum follow-up time of 5 years and a common exponential dropout rate of 0.0211 (assuming 10% 5-year drop-out rate in each group). The planned log-rank test should have similar power to the exponential MLE survival test.

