### Statistical methods

We will use a log rank test to compare PFS time between the two randomized treatment arms. We assume that approximately 13% of subjects randomized to Arm 2 will be found to be ineligible for SRT and will not be included for the primary endpoint analysis. Secondary analyses will utilize Cox-proportional hazards regression models. These models will include terms for treatment as well as appropriate clinical/demographic covariates (e.g., ADT, pelvic LN RT, PSA doubling time, Gleason grade, T stage, age, etc.). Residual analyses will be performed to evaluate the proportional hazards assumptions of the Cox model. As a sensitivity analysis, we will also consider survival models that can account for competing risks (ex. death from other causes).

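### The primary test drops scan-detected metastatic patients from Arm 2 only, so on its own it cannot show that PSMA PET/CT improves outcomes

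*Protocol article*

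**What the plan says.** Under Rationale for study design and hypothesis, the protocol article restricts the primary endpoint to patients who actually receive SRT: "Therefore, patients with PSMA PET/CT showing distant metastases will not be included for the primary endpoint analysis but will still be followed". The abstract, Salvage radiation therapy management and Statistical methods repeat the exclusion, at an assumed 13% of Arm 2.

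The same rationale concedes that control patients may carry hidden metastatic disease, "but these patients would still receive SRT per routine care". No matching exclusion is stated for Arm 1.

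Intention to treat is set aside for this reason: "An intention to treat analysis would classify subject who undergo PSMA PET/CT and are found to have distant metastases as failure", even though untreated. The test itself is described thus: "We will use a log rank test to compare PFS time between the two randomized treatment arms". The trial is labelled superiority, and the abstract calls it "designed to determine whether PSMA PET/CT molecular imaging can improve outcomes in patients with PCa early BCR following radical prostatectomy". The last paragraph of the main Discussion makes a similar claim.

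Two further provisions matter. Primary endpoint measure says: "Biochemical progression is defined as a serum PSA ≥ 0.2 ng/mL and rising after completion of SRT". Study duration ends follow-up when extra-pelvic metastasis is diagnosed by any imaging.

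**The concern.** The exclusion takes place after randomisation, depends on a test done in one arm, and selects on prognosis. The protocol itself holds that these patients do badly: the rationale says that SRT to standard volumes would give no durable response where lesions lie outside them. The Background cites a 99-patient series with response of 30% in PSMA M1 disease against 81% to 85% in fossa-confined or scan-negative disease.

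Removing such patients from one arm raises that arm's success rate without helping anyone. The rationale even counts the exclusion (13%) together with better coverage (7%) towards the hypothesised 20-point gain. At stake is whether a significant primary result can be read as benefit from the scan.

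**Working it through.** **Inputs from the protocol article.** 90 and 103 randomised; 5-year PFS 60% and 80%; two-sided alpha 0.05 with 80% power; 5 years of follow-up; 10% dropout at 5 years; 13% of Arm 2 excluded.

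**Assumption.** The 5-year BPFS of M1 patients after SRT is not given. I use 0% (the rationale's claim of no durable response) to 30% (the cited short-term M1 response, taken as an upper bound).

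**The plan's own figure.** Hazards are -ln(0.6)/5 = 0.1022 and -ln(0.8)/5 = 0.0446, ratio 0.437. Events = 4 × (1.960 + 0.842)² / (ln 0.437)² ≈ 46. The exponential test with 90 per arm gives 79.9% to 80.8% power, and 103 × 0.87 = 89.6, about 90. The stated design reproduces.

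**Effect of the exclusion alone.** Let the scan change nothing, with 60% overall BPFS and 13% M1 in both arms. With M1 BPFS s, the analysed part of Arm 2 shows (0.60 - 0.13s)/0.87. I simulated the log-rank test (20,000 trials per row; dropout hazard 0.0211; 0% entered as 0.5%):

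| M1 5-year BPFS | Arm 2 as analysed | Control | Gain (points) | Trials favouring Arm 2 |
|---|---|---|---|---|
| 0% | 69.0% | 60% | 9.0 | 28% |
| 10% | 67.5% | 60% | 7.5 | 19% |
| 30% | 64.5% | 60% | 4.5 | 9% |
| 60% (no prognostic difference) | 60.0% | 60% | 0 | 2.5% |

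The nominal rate is 2.5%. With all 193 analysed as randomised, the same scenarios give 2.6% to 3.1% (8,000 trials each). The last row confirms the mechanism: the excess vanishes when M1 patients do as well as the others. At the 0% end, 9.0 of the planned 20 points (45%) come from the exclusion.

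**All-randomised contrast.** If analysed Arm 2 patients truly reach 80% and every M1 patient fails, Arm 2 as a whole has 0.87 × 0.80 = 69.6% against 60%, a hazard ratio of ln(0.696)/ln(0.60) = 0.71. Power with 193 patients is about 26% to 28% (26.6% in simulation). Reaching 80% would need about 267 events, roughly 800 patients.

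**Can the existing secondary endpoint be computed?** BPFS from randomisation is listed. Progression, however, is defined only after completion of SRT, so a patient who never receives SRT could have no event other than death. Study duration, read literally, ends that patient's follow-up on the scan date, whereas the abstract and the rationale promise continued follow-up.

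**The case against.** **The question is openly stated.** The rationale asks about SRT success among patients for whom SRT is appropriate given their imaging, and it discloses the asymmetry. For that question 69% against 60% is a true difference. A reader might infer that the primary test simply fails to hold its 5% level. The documents do not support that without qualification: the excess arises when the result is read as an effect of the scan on outcomes.

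**The size depends on an unknown.** The 28% figure needs near-total failure in M1 patients; at 30% success it is about 9%. Routine imaging in controls could narrow the imbalance, and the phrase about patients who actually receive SRT is neutral between arms. But no exclusion is stated for Arm 1, and Salvage radiation therapy management excludes Arm 2 patients on the scan finding whatever treatment follows. Every value in the 0% to 30% range still inflates the rate.

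**The reason given against intention to treat has some substance.** Patients enter with PSA of at least 0.1 ng/mL, so a rule of 0.2 and rising, applied without SRT, could be met almost at once. A reader might infer that the reason is wholly mistaken; it is better called imprecise. Early events would come from the endpoint definition, not from intention to treat.

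**The secondary endpoint exists.** Its analysis population may properly be left to the analysis plan, so the population is not a finding. The definition tied to SRT and the conflicting follow-up rules are in the text and do stand.

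**Power.** Making the all-randomised comparison primary at this size would leave an underpowered trial. This stands, and it is why the fix limits the claim and does not replace the primary test.

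**Conclusion.** The primary comparison is not between randomised groups. With no effect of the scan on any patient it would show Arm 2 ahead by 4.5 to 9.0 points and favour Arm 2 in about 9% to 28% of trials instead of 2.5%. This rests on 13% M1 in both arms, 60% overall BPFS, and M1 5-year BPFS between 30% and 0%. The result can describe SRT success in differently selected patients. It cannot carry the claim in the abstract and the main Discussion that PSMA PET/CT improves outcomes.

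A reader might also infer, from the 7% attributed to better coverage, that the all-randomised figure in Arm 2 can be at most 67%. The documents do not fix such a ceiling: Sample size determination assumes 80% in Arm 2 with 90 eligible patients, which gives 69.6% even if every M1 patient fails, and more if some do not.

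**What to change.** 1. **Limit the claim.** State that the SRT-started comparison shows SRT success in differently selected patients. Any statement that the scan improves outcomes should rest on BPFS from randomisation in all 193 patients by assigned arm.
2. **Make that endpoint computable.** Define progression for patients who do not receive SRT, allowing for their PSA at entry and the early events it could produce. Reconcile the end of follow-up at M1 diagnosis in Study duration with the promise of continued follow-up in the abstract and the rationale.
3. **Add a bounding analysis.** Remove from the control arm the worst outcomes equal to the M1 share seen in Arm 2, and compare Arm 2 with that trimmed curve. If all those removed are failures, the expected control value is 0.60/0.87 = 69.0%. If 30% of the removed share are successes, it is (0.60 - 0.039)/0.87 = 64.5%. The benchmark is therefore about 64.5% to 69%, not 60%. Report this as a bound, not as a test.
4. **Correct the intention-to-treat sentence.** Intention to treat keeps patients in their assigned arm and counts events when they occur; it does not in itself make diagnosis a failure.

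**Cost.** Wording, one endpoint definition, one added analysis, and continued follow-up of about 13 patients (103 × 0.13), which is already promised. The real downside is power: about 70% against 60% with about 26% to 28% power. The all-randomised result will probably be inconclusive and should be reported as an estimate with its confidence interval.

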### Objective of the trial

To evaluate the success rate of salvage radiation therapy (SRT) for recurrence of PCa after prostatectomy with and without planning based on PSMA PET/CT.

### Trial design

Interventional Phase III Randomized Controlled Parallel Assignment Prospective Open Label Clinical Trial.

*Allocation Ratio*: 1:1.13 ratio

*Framework:* Superiority

## Methods

### Study population

Patients with recurrence of PCa after primary radical prostatectomy.

It is anticipated that a total of 193 subjects will be recruited. Such a number is considered appropriate to achieve statistical power for the endpoints of this clinical trial.

*Inclusion criteria*:Histopathology proven PCaPlanned SRT for recurrence after primary prostatectomyPSA ≥ 0.1 ng/ml at time of enrollmentWillingness to undergo radiotherapy.Treating radiation oncologist intends to incorporate PSMA PET/CT findings into the radiotherapy plan if patient undergoes PSMA PET/CT

*Exclusion criteria*:Extra-pelvic metastasis on any imaging or biopsyAndrogen deprivation therapy (ADT) within 3 months before PSMA PET/CTContraindications to radiotherapy (including active inflammatory bowel disease)Concurrent systemic therapy for PCa with investigational agents.

### Intervention

#### Study procedure

Patients allocated to the PSMA SRT arm (arm 2) will undergo one PSMA PET/CT scan at the UCLA Nuclear Medicine clinic before SRT planning.

#### Investigational PET imaging drug

We will use ^68^Ga-PSMA-11 (Gallium-68-labeled PSMA-ligand Glu-urea-Lys(Ahx)-HBED-CC) as the PET radiopharmaceutical. The administered activity is 3–7 mCi i.v.

#### Source of the study drug

UCLA Biomedical Cyclotron, [name]; Ga-generator generator from Eckert and Ziegler Isotope Products.

#### PET/CT imaging protocol specific

Oral hydration and voiding are recommended immediately before start of the scan. Oral contrast and IV contrast will be administered if not contraindicated. PET/CT images will be obtained using the Siemens Biograph 64 and mCT scanners and will be acquired in 3D mode at 50–100 min after injection of 3–7 mCi of ^68^Ga-PSMA-11. Scan coverage will extend from mid-thigh to the vertex, starting from the mid-thighs. A minimum of 3 min per bed position will be used (weight-based protocol) [49]. Attenuation correction of PET emission data is using segmented CT data. PET images are reconstructed using ordered subset expectation maximization (OSEM) with 2 iterations and 8 subsets.

#### PET/CT imaging analysis

PET/CT Images will be reviewed and analyzed using Siemens Syngo/TrueD and OSIRIX workstations by a board certified nuclear medicine physician and a board certified radiologist experienced in reading PET/CT using recent reporting guidelines (PROMISE criteria, miTNM standardized framework) [50].

#### PET/CT DICOM images transfer

CD/DVD containing the PSMA PET/CT DICOM images and PET/CT report will be delivered to the treating radiation oncologist.

#### Salvage radiation therapy management

The treating physician will be asked to describe their general treatment plan prior to randomization. The choice of treating the prostate bed alone vs prostate bed and pelvic lymph nodes, with or without ADT, is at the discretion of the treating physician.

Patients randomized to control arm 1 do not undergo PSMA PET/CT: SRT will be performed as routinely planned per discretion of the treating radiation oncologist in accordance with the initial general treatment plan whenever possible. Any other imaging is allowed for SRT planning if done per routine care.

Patients randomized to arm 2 will undergo a PSMA PET/CT scan before SRT planning.If the PSMA PET/CT scan is negative for BCR site identification: SRT will be performed as routinely planned per discretion of the treating radiation oncologist in accordance with the initial general treatment plan whenever possible. The treating physician is encouraged not to de-escalate therapy as a negative PSMA PET/CT does not mean that the patient has no recurrent PCa, rather that it was unable to be detected by the scan (for example, microscopic disease). Thus, if the initial treatment intent was to treat the prostate bed and pelvic nodes, then this should be pursued even in the absence of PSMA-positive nodes.if the PSMA PET/CT scan is positive for pelvic lesions: SRT can be performed with adapted/extended target volumes to include all pelvic PSMA-positive lesions within the radiation fields. SRT may also be performed with focal dose escalation on the PSMA-positive lesions if feasible. SRT can also be performed as routinely planned in accordance with the initial general treatment plan per discretion of the treating radiation oncologist. Furthermore, a PSMA PET/CT scan showing PSMA-positive disease in one or more pelvic nodes does not exclude the possibility of additional disease in the prostate bed, and vice versa.If the PSMA PET/CT scan detects PSMA-positive lesions outside the pelvis: Treatment management will be performed as per discretion of the treating radiation oncologist. We assume that approximately 13% of subjects randomized to Arm 2 will have PSMA-positive distant metastases. These patients will not be included in analysis of the primary endpoint, and their actual treatment plan will be determined by the treating radiation oncologist.

### Outcome measures

#### Primary endpoint measure

Success rate of SRT measured as rate of biochemical progression-free survival (BPFS) after initiation of SRT (Time Frame: From date of initiation of SRT until the date of first documented progression or death from any cause, whichever comes first, assessed up to 5 years). Biochemical progression is defined as a serum PSA ≥ 0.2 ng/mL and rising after completion of SRT (second confirmatory value must be rising and separated by ≥ 1 month).

#### Secondary endpoints measures

5-year BPFS rate from date of randomization (Time Frame: 5 years)Metastasis free-survival from date of randomization (Time Frame: 5 years). Diagnosis of extra-pelvic metastatic (M1) disease can be obtained by any imaging or biopsy.Initiation of additional salvage therapy after completion of SRT measured as rate of additional PCa therapy initiation-free survival (Time Frame: 5 years; from the initiation of SRT until the first documented initiation of any additional PCa treatment).Change in initial treatment intent.

### Timeline

#### Screening and enrollment

Patients seen for consultation in a radiation oncology, urology, or nuclear medicine clinic who are being evaluated for potential SRT will be informed of this clinical study. The decision to participate will be entirely voluntary. All subjects must sign and personally date the IRB approved informed consent form (ICF) after receiving detailed written and verbal information about the reason, the nature and the possible risks of the trial.UCLA patients will consent after a thorough discussion between the patient and the consenting UCLA physician.All other patients (outside UCLA) will consult over the phone with the UCLA nuclear medicine research team to discuss the study protocol. Signed ICF will be obtained by fax or email.To register and enroll a patient, the UCLA nuclear medicine research coordinator will obtain all required medical documentation, signed informed consent and signed Health Information Portability and Accountability Act (HIPAA) authorization form (by fax or email if patient is from outside UCLA).

#### Randomization and intervention

5)Enrolled patients will be randomized to either the control arm (arm 1) or the PSMA SRT arm (arm 2) in a 1:1.13 ratio. The randomization number and assigned arm will be communicated by phone or email to treating physicians and patients 1 day after the enrollment.6)Patients assigned to arm 2 will be scheduled to undergo a PSMA PET/CT scan at UCLA Nuclear Medicine free of charge prior to radiation therapy planning. DICOM images and reports of PSMA PET/CT scans will be delivered to the treating radiation oncologist.7)SRT will be done per routine care at the treating radiation oncologist institution, and typically takes place over about 2 months. The treating radiation oncologist may change the radiation plan depending on the findings of the PSMA PET/CT scan.

#### Follow-up

Current standard-of-care includes weekly on treatment visits during radiotherapy followed by follow-up visits with radiation oncologist at least every 3 to 4 months for the first year and every 6 months for the next 5 years.

Total serum PSA measurements are obtained during follow-up visits per standard-of-care. Biochemical progression is defined by PSA ≥ 0.2 ng/mL and rising after completion of SRT (second confirmatory value must be rising and separated by ≥ 1 month). Additional labs are drawn per the discretion of the treating physician.

Imaging studies are done at the discretion of the treating physicians. Imaging is typically initiated at the time of suspected biochemical or clinical recurrence, and may include CT, MRI, or PET. The treating physician decides if biopsy confirmation is necessary or not.

UCLA Nuclear Medicine Research investigators or their staff will conduct telephone follow-up with enrolled patients at 3–4-month intervals for the first year and then at 6-month intervals. The investigators or staff will ask the patient for their most recent PSA value and the draw date, if and when any additional salvage therapy has been initiated, and if and when any imaging studies suggest radiographic progression. Research investigators or their staff may also conduct telephone or secure email follow-up with the treating physicians to identify changes to the initial general treatment plan (prostate bed alone, prostate bed with ADT, prostate bed and nodes, prostate bed and nodes with ADT). The study team may request more details about the actual radiation treatment plan at the discretion of the patient and the treating physician. Although we acknowledge that toxicity assessments, both patient reported and physician reported, are valuable components of prospective trials, the design of the trial makes rigorous assessments of these difficult.

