#### Study duration

We expect to enroll the 193 patients within 2 years of study initiation. Patients will be followed by UCLA Nuclear medicine (phone calls/ secure emails) until either one of the following conditions occur:5 years after the date of initiation of randomization.Biochemical progression.Diagnostic of extra-pelvic metastatic disease by any imaging or biopsy.Initiation of any additional salvage therapy.Death.

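### Each follow-up call asks for one latest PSA, while the primary event needs two dated values, so some progressions may be dated late or be impossible to document

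*Protocol article*

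**What the plan says.** Three parts of the protocol article bear on this point.

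- **Event.** Under Primary endpoint measure, time runs "From date of initiation of SRT until the date of first documented progression or death from any cause, whichever comes first". Biochemical progression is a PSA of at least 0.2 ng/mL and rising after completion of SRT, and the "second confirmatory value must be rising and separated by ≥ 1 month". Additional salvage therapy is not part of this event. It has its own entry under Secondary endpoints measures.
- **Data capture.** Under Follow-up, the study team will "conduct telephone follow-up with enrolled patients at 3–4-month intervals for the first year and then at 6-month intervals". At each contact they "ask the patient for their most recent PSA value and the draw date", and they also ask for the dates of any additional salvage therapy and of imaging that suggests progression. Staff may also make "follow-up with the treating physicians to identify changes to the initial general treatment plan"; retrieval of PSA history is not named as a purpose.
- **End of follow-up.** Study duration lists "Initiation of any additional salvage therapy" among the conditions that end a patient's follow-up.

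Follow-up also describes routine visits "at least every 3 to 4 months for the first year and every 6 months for the next 5 years", with PSA drawn at visits.

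**The concern.** The endpoint is defined on a pair of dated values, but the stated question yields one value per contact. If two or more draws fall between contacts, only the last is asked for. If further therapy has also started, the last value may be a post-therapy one, and no later contact follows.

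At stake is whether a real progression can be shown to meet the definition, and on what date. This matters because the primary analysis is a log-rank test with a modest planned event count. Values not collected while a patient is being followed may be hard to recover later.

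**Working it through.** **1. The plan's own figure.** Inputs from Sample size determination: 90 eligible patients per arm, 5-year failure of 40% and 20%, 10% dropout over 5 years, 80% power and a "0.050 two-sided significance level".

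- Hazards: −ln(0.6)/5 = 0.1022, −ln(0.8)/5 = 0.0446 and, for dropout, −ln(0.9)/5 = 0.0211. The hazard ratio is 0.4368 and its log is −0.828.
- Events needed (Schoenfeld): 4 × (1.960 + 0.842)² / 0.828² ≈ 45.8, so 46. The stated figure reproduces.
- The exponential test with 90 per arm gives power of 0.799 to 0.808, depending on the variance form. The stated 80% also reproduces.

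**2. Events expected if every progression is documented.** The probability of an observed event over 5 years is h/(h + d) × (1 − exp(−5(h + d))), where h is the event hazard and d the dropout hazard.

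- Control: 0.1022/0.1232 × (1 − 0.54) = 0.381; × 90 = 34.3.
- PSMA: 0.0446/0.0657 × (1 − 0.72) = 0.190; × 90 = 17.1.
- Total 51.4, which is 5.4 above 46; 5.4/51.4 = 10.5%.

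**3. What the stated question records in each situation.**

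| Situation | What the calls record | Result |
|---|---|---|
| Draws only at scheduled visits, no therapy between calls | One new dated value per call | Pair assembled over two calls |
| Unscheduled confirmatory draw between calls, no therapy | Confirmatory value only, then a later value | Progression documentable, but dated late |
| Both draws and start of therapy between calls, no PSA since | Confirmatory value and therapy date | One qualifying value; follow-up ends |
| As above, with a PSA after therapy started | Post-therapy value and therapy date | Neither qualifying value; follow-up ends |

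In the second row the delay is less than one call interval, because draw dates are asked for and the next call picks up the latest value.

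**4. How often a call would catch the first value when confirmation is unscheduled.** Assume that the first qualifying draw falls uniformly within a call interval of L months and that the confirmatory draw comes c months later. A call falls between the two draws with probability min(1, c/L).

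| c (months) | L = 3.5 | L = 6 |
|---|---|---|
| 1 | 29% | 17% |
| 2 | 57% | 33% |
| 3 | 86% | 50% |
| 6 | 100% | 100% |

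These probabilities apply only to patients with an early confirmatory draw. They are not rates of lost events. The document does not say how many patients have such a draw.

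**5. Illustration of size.** If 10% of the 51.4 events could not be documented and were not counted, 46.3 would remain. Schoenfeld power, Φ(√E/2 × 0.828 − 1.96), would move from 84.4% at 51.4 events to 80.4% at 46.3. The margin exists only on the Schoenfeld count. On the plan's exponential test, 90 per arm gives about 80% with all 51.4 events, which leaves nothing to spare.

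**The case against.** The strongest reply is that visits and calls share a schedule. The latest PSA at a call is then usually the only one since the previous call, and the calls build a dated series. This stands, and it confines the problem to unscheduled draws and to therapy started between calls.

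A second reply is that the same call asks when salvage therapy began and whether imaging suggests progression, so these patients are noticed and could prompt retrieval of earlier values. This stands in part. The therapy date is captured, but it does not supply the PSA pair, and retrieval is not described.

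A third reply is that call scripts and database fields belong to the full protocol, which an article condenses. That would answer a complaint about missing detail. Here, however, the article states what is asked, and what it states does not match the endpoint it defines.

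Three stronger readings are tempting but not supported:

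- **Patients are censored at salvage therapy and their events lost.** The article gives no such rule. How therapy without a confirmed rise enters the primary analysis may be settled in the SAP.
- **Power falls by a particular amount.** No rate of undocumented progression is given, so any such figure rests on a chosen rate.
- **The loss differs by arm because the trial is open label.** Nothing in the document gives a direction or size for this.

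**Conclusion.** The mismatch is in the text: a two-value event, one value asked for per contact, and follow-up that ends at a therapy which is not itself a primary event. Where a confirmatory draw or salvage therapy falls between calls, a progression may be dated late, or may not be documentable as defined. Where draws keep to the visit schedule and no therapy intervenes, the stated procedure works.

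The frequency is unknown. The only size that can be given is how little room there is: 51.4 expected events against 46, or about 10%. This rests on the plan's hazards and dropout, a full 5 years of observation per patient and the Schoenfeld count. It shows sensitivity and does not forecast a loss. The point is worth acting on because the remedy is cheap and protects the primary endpoint.

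**What to change.** In Follow-up, replace the request for the latest PSA with a request for every PSA value and draw date since the previous contact, including those drawn before any salvage therapy, and hold them in a repeating REDCap field. State one rule for dating progression, for example the first qualifying value once it is confirmed.

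The cost is slightly longer calls and more data entry. No visit, test or treatment decision changes.

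There is one limit. If therapy starts after a single unconfirmed PSA of at least 0.2 ng/mL, no confirmatory value exists to be collected. That case needs an analysis rule, and the team should check that the SAP contains one.
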